## Objectives

The ECHO study has four primary objectives described below:The primary obstetric objective is to establish whether infants born to women who vape are at a higher or lower risk of adverse outcomes in pregnancy compared to infants of combustible cigarette smokers and non-smokers.The primary neonatal objective is to assess anthropomorphic variation, if any, in newborn babies born to vapers in comparison to smokers and controls. The primary paediatric objective is to establish whether parent-reported and doctor-confirmed wheeze and/or asthma occurs more frequently in children exposed to vaping in utero compared with children of combustible cigarette smokers and non-smokers.The primary neurocognitive objective is to assess if there are significant differences in neurocognitive outcomes between the infants of a women who vape compared to infants of women who used combustible cigarette smokers and non-smokers.Globally, we aim to correlate, obstetric, neonatal, pulmonary, growth and neurocognitive differences, if any, to quantitative levels of cotinine excreted in maternal urine at in the third trimester.

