### Sequence of questionnaire timepoints

At recruitment to assess baseline cigarette smoking and vaping historyAfter 20 weeks/mid-trimesterThird trimesterAfter birthAged 6 monthsAged 1 yearAged 2 years

Self-administered, digital questionnaires, accessed on a smartphone, laptop or PC, are completed by participants without the presence of an interviewer; this may increase the validity of the reported exposure, hence the decision to prefer this method [36] when gathering data on frequency, duration and reasons for vaping. Questionnaires included validated instruments (Fagerstrom) to assess nicotine dependence in both cigarette smokers and vapers [37, 38]. Infants of study participants in exposure and control groups will be assessed at 12 and 24 months corrected for gestational age at birth.

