### Inclusion criteria

Women aged 18 or greater and less than 46 years of age at booking.Pregnant with a singleton fetus.Smoker or vaper or smoker/vaper or control.Able to understand and read English.Willing to agree to follow-up for the 2-year duration of the study in the postnatal period

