## Outcomes

### Primary outcomes

The primary outcomes outlined in Table 2 have informed the sample size calculation. As the outcomes for the postnatal psychological assessments are exploratory, we have used a pragmatic sample target of 150.

**Table 2. Tab2:** Primary outcomes

Primary outcomes		
Obstetrics/neonatal	Paediatrics	Psychology
• Preterm birth • Low birth weight	• Doctor-diagnosed wheeze	• Neonatal Behavioural Assessment Scale • Bayley’s Infant and Toddler Development (*n*=150)

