**Table Taba:** 

Women who vape during pregnancy will be more likely have a preterm birth and that their infants will have a lower birth weight (LBW), lower neuro-behavioural scores and increased respiratory symptoms when compared with non-smokers.
Women who vape during pregnancy will be less likely to have a preterm birth and their infants will have a higher birth weight, higher neuro-behavioural scores, and fewer respiratory symptoms than when compared with tobacco smokers.

The best available data suggest a prevalence of smoking rate during pregnancy in Ireland is between 9 and 10% [44], whilst the current expected rate of vaping during pregnancy is approximately 5% [45]. The cumulative live birth rates in the three maternity hospitals in Dublin in 2023 were: The Coombe Hospital—6974, The Rotunda Hospital—8442, and the National Maternity Hospital—6880, which will give a projected denominator of approximately 22,000 total live births. The incidence of vaping during pregnancy in the Coombe is 5% [34, 46]; projected to the other three hospitals gives approximately 750–1250 vapers per annum. The calculations in Table 3 give the magnitude of a detectable association with (2-year) prevalence of each condition (odds ratios) or mean differences that are detectable at a power of 80%, with a type I error rate of 0.05. These assume use of simple uncorrected Chi-square test or *t* tests. Detectable effect sizes are presented assuming a range of sample sizes to illustrate how power is maintained under a range of recruitment scenarios. We plan to collect three equally sized groups—non-smokers, smokers, and vapers

**Table 3 Tab3:** Sample size calculation

Sample size (per group)	Baseline incidence		
	10% (wheeze)	6.2% (preterm birth)	5% (low birth weight)
	Detectable odds ratios:		
100	3.00	3.62	3.19
200	2.25	2.63	2.26
300	1.96	2.24	1.91
**400**	**1.80**	**2.04**	**1.74**

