Whilst robust data on the effect of vaping during pregnancy on women and infants are lacking, the effects of smoking are well characterised on neonatal anthropometric measurements. Asthma or wheeze has an incidence of approximately 10% within the first 3 years of life [47]. LBW occurs at a frequency of about 5% [48]. PTB occurs in approximately 6.2% of births in Ireland [49]. Maternal smoking has been shown to increase risk of asthma or wheeze in childhood with an odds ratio of 1.8 (95% CI 1.35–2.53). Smoking has also been shown to increase incidence of LBW with an odds ratio of 1.75 (95% CI 1.42–2.10). The odds ratio for PTB conferred by smoking is 1.27 (95% CI 1.20–1.33).

Data on neurocognitive outcomes is lacking; neurocognitive outcomes between groups can be expressed as standardised mean differences (SMD). Table 4 gives indicative detectable differences for each sample size. For reference, caregiver depression has been as a risk factor on the NBAS with a SMD of 0.28 [50] and smoking demonstrated an association of the order of SMD = 0.2–0.4 for executive function including inhibition and self-control [51].

**Table 4 Tab4:** Indicative detectable differences per sample size

Sample size (per group)	Standardised mean difference
100	0.40
200	0.28
300	0.23
**400**	**0.20**

Therefore, we propose to recruit 1200 participants (400 smokers, 400 vapers and 400 non-smoker, non-vaper controls) to generate adequate power and precision to answer our research questions.

In the case that key measurements are missing at rates in excess of 5%, multiple imputation procedures will be considered. We anticipate the likelihood of missing data is small given the standard procedures in place to manage the study centrally.

Case report form (CRF) data entry into REDCap will include extensive data validation checks. Missing data will be monitored, and strategies will be developed to minimise its occurrence. Central statistical data monitoring will summarise missing or inconsistent data periodically. The study workbook will be approved by the chief investigator and validations will also be made that will cross-check the study workbook with the ECHO study electronic CRF.

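### The detectable odds ratio of 1.80 for wheeze is a best case: its 10% baseline covers 3 years, follow-up covers 2, and all 400 recruits per group are counted as evaluable

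*Protocol article*

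**What the plan says.** All of this is in the protocol article.

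- **Horizon of the power figures.** Under *Power calculations and rationale*, the calculations in Table 3 "give the magnitude of a detectable association with (2-year) prevalence of each condition". The test is an uncorrected chi-square, with 80% power and type I error 0.05.
- **Baseline.** Table 3 uses 10% for wheeze. The text after the table explains it: "Asthma or wheeze has an incidence of approximately 10% within the first 3 years of life".
- **Follow-up.** Under *Sequence of questionnaire timepoints*, infants "will be assessed at 12 and 24 months corrected for gestational age at birth". The matching inclusion criterion is "Willing to agree to follow-up for the 2-year duration of the study in the postnatal period".
- **Outcome.** Table 2 lists "Doctor-diagnosed wheeze" as the paediatric primary outcome. *Objectives* words it as "parent-reported and doctor-confirmed wheeze and/or asthma".
- **Numbers.** The bold row of Table 3 is 400 per group with a detectable OR of 1.80 for wheeze. The plan is to recruit 1200 women, 400 per group, before 24 weeks' gestation. The OR cited for maternal smoking and asthma or wheeze is 1.8.
- **Loss.** No attrition figure is given. The text says: "We anticipate the likelihood of missing data is small given the standard procedures in place to manage the study centrally". Multiple imputation will be considered if key measurements are missing at rates above 5%.
- **Robustness.** The text presents the range of sample sizes as showing that power holds up across recruitment scenarios.

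**The concern.** Two inputs to the wheeze column do not match the design, and each departs from it in the favourable direction.

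First, the baseline is a 3-year figure applied to an outcome observed for 2 years. Cumulative incidence cannot fall with time, so for one population and one definition the 2-year rate is at most the 3-year rate.

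Second, the number entered in the calculation is the number recruited in pregnancy. The outcome is ascertained up to age 2, and some infants leave the study by design, for example after a newborn-screening diagnosis listed under *Exclusion criteria*. The reason given for expecting little missing data is central study management, which does not bear directly on families leaving over more than two years.

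The chosen row gives exactly the cited smoking OR, so there is no margin to absorb either departure. A reader of a null wheeze result could then credit the study with 80% power to detect an OR of 1.8 when its power was lower.

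**Working it through.** **Inputs from the document.** Baseline p1 = 10%; n = 400 per group, equal groups; uncorrected chi-square; type I error 0.05; power 80%; reference OR 1.8. Sidedness is not stated; a two-sided test is used because it reproduces the table.

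**Formulas.** Rate in the comparison group: p2 = p1·OR / (1 − p1 + p1·OR). With p̄ = (p1 + p2)/2,

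n per group = [1.96·√(2p̄(1 − p̄)) + 0.8416·√(p1(1 − p1) + p2(1 − p2))]² / (p2 − p1)².

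**Step 1: reproduce the plan's figure.** For p1 = 0.10 and OR 1.8, p2 = 0.18/1.08 = 0.1667, p2 − p1 = 0.0667 and p̄ = 0.1333. The two square roots are √0.2311 = 0.4807 and √0.2289 = 0.4784. Then n = (0.9422 + 0.4026)² / 0.004444 = 407. With n = 400, z = (0.06667 × 20 − 0.9422)/0.4784 = 0.817, which is 79.3% power. Solving for 80% power gives these detectable ORs:

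| n per group | Table 3 | Recalculated |
|---|---|---|
| 100 | 3.00 | 2.99 |
| 200 | 2.25 | 2.25 |
| 300 | 1.96 | 1.96 |
| 400 | 1.80 | 1.81 |

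The column reproduces. At 400 per group it meets the 1.8 reference with nothing to spare.

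**Step 2: vary the two inputs.** The document gives neither a 24-month rate nor a loss rate, so both are assumptions here. Loss d enters as n = 400(1 − d). The lowest baseline, 6.7%, is 10% × 2/3, which assumes linear accrual over 3 years. Cells show the detectable OR at 80% power, with power at OR 1.8 in brackets.

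| Baseline at 24 months | No loss (400) | 5% loss (380) | 10% loss (360) | 20% loss (320) |
|---|---|---|---|---|
| 10% | 1.81 (79%) | 1.83 (77%) | 1.86 (75%) | 1.93 (70%) |
| 9% | 1.85 (76%) | 1.88 (74%) | 1.91 (71%) | 1.98 (66%) |
| 8% | 1.91 (71%) | 1.93 (69%) | 1.97 (67%) | 2.04 (62%) |
| 6.7% | 2.00 (65%) | 2.03 (62%) | 2.06 (60%) | 2.15 (55%) |

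**Step 3: the robustness sentence.** Table 3 holds power at 80% by construction and lets the detectable OR move. In the wheeze column it moves from 1.80 at 400 per group to 1.96 at 300. At 300 per group, power for OR 1.8 is 67%. So the table shows the detectable effect growing as numbers fall; it does not show power being preserved for a fixed effect.

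**The case against.** The case on the other side has several parts.

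- **The arithmetic is sound.** This stands. A reader might infer that the wheeze column is miscalculated; it is not. The fault lies in the inputs.
- **The 2-year rate may be close to 10%.** This stands. A reader might infer that the 24-month rate is known to be below 10%. The document gives no such rate, and the 10% is itself approximate. It says only enough to make 10% a ceiling for the same outcome. The 6.7% row rests on linear accrual, which nothing in the document supports, so the figures in that row illustrate the range and predict nothing.
- **Loss may be small, and part of it recoverable.** This stands in part. At 5% loss alone the change is slight (1.83, 77%). Wheeze is also recorded at 6 and 12 months and the planned analysis is longitudinal, so children lost before 24 months still contribute. Imputation may help too. Scaling n by retention therefore probably overstates the lost information, but neither device generally restores 400 fully observed children.
- **OR 1.8 is not a declared target.** It is a smoking reference, while the exposure of interest is vaping, for which the document says robust data are lacking. True, but the smoking ORs are the only effect sizes offered for judging the binary columns, and the recommended row matches this one.
- **A reader can already see the cost.** The 300 row does show it for numbers, though it is presented as a recruitment scenario. No row shows the effect of a lower baseline.
- **The outcome wording.** A reader might infer three conflicting primary outcomes. Table 2's entry is a short label, and *Objectives* also requires a doctor's confirmation, so this is mostly wording. What remains is that the 10% is for asthma or wheeze, while Table 2 names wheeze alone.

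A reader might also take wheeze to be the only binary primary outcome that appears powered for a smoking-sized effect. As printed it is not: low birth weight is shown at 1.74 against a cited 1.75.

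**Conclusion.** The point holds as a mismatch of inputs. The baseline covers 3 years for an outcome followed for 2, and recruited numbers stand in for evaluable ones. The direction of each is clear: a lower 24-month rate or any net loss of information raises the detectable OR above the stated value. The 1.80 is therefore a best case relative to the study's own 10% figure.

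The size is not fixed by the document. Under the assumed ranges it runs from slight (OR 1.83 and 77% power at OR 1.8, with 5% loss and a full 10% baseline) to material (OR 2.04 and 62% power, with an 8% baseline and 20% loss). These figures rest on a two-sided, uncorrected, single-time comparison of two equal groups, as Table 3 does. They do not credit earlier wheeze reports or imputation. The document does not support a firm statement that the study will be badly underpowered for wheeze.

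**What to change.** 1. Restate the wheeze column of Table 3 with a 24-month rate for the outcome named in Table 2. If no such rate is available, show a range with 10% as its top.
2. State the number expected to be evaluable at 24 months and base the recommended row on that number instead of on the 400 recruited.
3. Replace the sentence on power across recruitment scenarios with one saying that the detectable OR rises as numbers fall, for example to 1.96 at 300 per group.
4. Use one wording for the wheeze outcome in *Objectives*, Table 2 and the power text.

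The cost is one recalculated column and some rewording. The downside is a less favourable stated OR. Recruitment, outcomes and analysis do not change.

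### For preterm birth, 400 per group gives about 14% power at the only effect size the protocol cites (odds ratio 1.27), so the unqualified claim of adequate power does not hold for this primary outcome

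*Protocol article*

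**What the plan says.** Table 2 (Primary outcomes) lists preterm birth with low birth weight under obstetrics/neonatal, and the text above it states: "The primary outcomes outlined in Table 2 have informed the sample size calculation".

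Under Power calculations and rationale, Table 3 shows odds ratios "detectable at a power of 80%, with a type I error rate of 0.05". The tests assumed are the chi-square test without correction for proportions and the *t* test for means. For preterm birth, at a baseline of 6.2%, the detectable odds ratio at 400 per group is 2.04.

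The text after Table 3 gives the effect of smoking on each binary outcome: 1.8 for asthma or wheeze, 1.75 for low birth weight and, for preterm birth, "The odds ratio for PTB conferred by smoking is 1.27 (95% CI 1.20–1.33"). No odds ratio for vaping is given. A neurocognitive paragraph and Table 4 follow, and then the conclusion that 1200 women should be enrolled, 400 in each of the three groups. The stated purpose of that number is "to generate adequate power and precision to answer our research questions".

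The two hypotheses expect vapers to have more preterm birth than non-smokers and less than tobacco smokers.

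**The concern.** The closing statement covers all the research questions without exception. For preterm birth, the detectable odds ratio of 2.04 lies far above the cited 1.27 and well outside its interval of 1.20 to 1.33. The text does not remark on the gap.

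The printed values for wheeze (1.80 against 1.8) and low birth weight (1.74 against 1.75) line up with the cited smoking effects. A reader could therefore assume that preterm birth is covered in the same way.

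At stake is how a non-significant preterm result is understood. The Dissemination section expects the findings to inform guidelines. With the power actually available, such a result could not separate no effect from an effect as large as the one cited for smoking.

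**Working it through.** **Inputs, all from Power calculations and rationale**
- Baseline preterm rate p0 = 0.062.
- n = 400 per group, equal groups.
- Type I error 0.05. Sidedness is not stated. Two-sided is assumed because Table 3 reproduces that way; one-sided would give 1.90, not 2.04.
- Uncorrected chi-square test, with no allowance for multiplicity or dropout.
- Cited smoking odds ratio (OR) 1.27, interval 1.20 to 1.33.

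**Formulas**
- Comparison rate: p1 = OR × p0 / (1 − p0 + OR × p0).
- With d = p1 − p0 and p̄ = (p0 + p1)/2: s0 = √(2p̄(1 − p̄)/n) and s1 = √(p0(1 − p0)/n + p1(1 − p1)/n).
- Power = Φ((d − 1.96 s0)/s1) + Φ((−d − 1.96 s0)/s1).

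**Step 1: reproduce the plan's figure.** At OR 2.04, p1 = 0.1188, d = 0.0568, s0 = 0.0203 and s1 = 0.0202. Power = Φ(0.846) = 80.1%. Solving for exactly 80% gives OR 2.038. The other preterm rows come out at 3.63, 2.62 and 2.24, against the printed 3.62, 2.63 and 2.24. The preterm column is sound.

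**Step 2: power at the cited effect.** At OR 1.27:
- p1 = 1.27 × 0.062 / (0.938 + 1.27 × 0.062) = 0.0774, so d = 0.0154.
- s0 and s1 are both about 0.0180.
- Power = Φ(−1.103) + Φ(−2.819) = 0.135 + 0.002 = 13.7%. Exact enumeration of the uncorrected chi-square test also gives 13.7%.
- Expected events: 400 × 0.062 = 24.8 against 400 × 0.0774 = 31.0.

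| Odds ratio | Comparison rate | Power, 400 per group | n per group for 80% |
|---|---|---|---|
| 1.20 | 7.35% | 9.9% | 7,510 |
| 1.27 | 7.74% | 13.7% | 4,268 |
| 1.33 | 8.08% | 17.8% | 2,942 |
| 2.04 | 11.88% | 80.1% | 399 |

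Alternative conventions do not change the picture at 1.27. A one-sided test gives 21.6%, a continuity correction gives 10.7%, and reading 1.27 as a risk ratio gives 15.0%.

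**Step 3: precision.**
- No true effect: SE(log OR) = √(2/(400 × 0.062 × 0.938)) = 0.293. Expected 95% interval = exp(±1.96 × 0.293) = 0.56 to 1.78.
- True OR 1.27: SE = √(1/(400 × 0.0620 × 0.9380) + 1/(400 × 0.0774 × 0.9226)) = 0.279. Expected interval = 1.27 × exp(±1.96 × 0.279) = 0.73 to 2.20.

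Both intervals contain 1.00 and 1.27.

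**Step 4: from smokers to vapers.** The 13.7% is strictly the power of smokers against controls. If the vaper rate lies between 6.2% and 7.74%, neither vaper contrast can exceed the control-to-smoker gap, so each has about 14% power or less. In the limiting case where vaping equals smoking, vapers against controls have 13.7% power and an 86.3% chance of a non-significant result.

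**The case against.** Several points on the other side are fair.

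- **Nothing is miscalculated or hidden.** Table 3's preterm column is right, and 2.04 and 1.27 are both printed. A reader might infer an arithmetical error, and there is none. The fault is a concluding sentence broader than its figures support.
- **The conclusion is about all outcomes together.** It comes after the neurocognitive paragraph and Table 4 and is not a specific statement about preterm birth. For wheeze, 400 per group does have a basis: 1.80 against a cited 1.8, with about 79% power. But the sentence is unqualified, and preterm birth is a named primary outcome said to have informed the sample size.
- **1.27 is a smoking effect.** The hypotheses give directions without magnitudes, and the primary obstetric objective leaves open higher or lower risk. The text also says that robust vaping data are lacking. A reader might take 14% as the power for vapers outright. The documents support that only conditionally, through the hypothesised ordering. Nothing in them points to an effect near 2.04, however.
- **Interpretation rules may sit in the analysis plan.** Their absence from the article is not the fault. The adequacy statement is made in the article and needs correcting there.

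A reader might also infer that a non-significant result is close to certain, or that the investigators intend to report one as reassurance. The first is too strong: the chance is about 86% at 1.27 and 82% at 1.33. The second has no support in the text, which commits to STROBE reporting.

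**Conclusion.** The point stands in a limited form: the claim of adequate power and precision does not hold for preterm birth on the protocol's own figures. Eighty per cent power is reached only at an odds ratio of 2.04. At the cited 1.27, 80% power would need about 4,270 per group, more than ten times the planned 400.

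This rests on a two-sided 0.05 uncorrected test, a 6.2% baseline and complete data on 400 per group; dropout or a multiplicity adjustment would lower power further. Extending it to the vaper contrasts also assumes that vapers lie between controls and smokers and that 1.27 applies to this study's smokers. The finding concerns one outcome and one sentence. It does not show that the sample size is unsuitable for every outcome, or that Table 3's preterm figures are wrong.

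**What to change.** In Power calculations and rationale, revise the concluding sentence as follows:
- Limit the adequacy statement to the outcomes for which it holds. Check each one first: the low-birth-weight column of Table 3 does not reproduce at its stated 5% baseline (2.17 computed against 1.74 printed at 400 per group), so that outcome should not be cited as covered without rework.
- State that 400 per group is not sized on preterm birth. Power is about 14% at an odds ratio of 1.27 (10% to 18% over the cited interval) and reaches 80% only at 2.04. The expected 95% confidence interval under no effect is about 0.56 to 1.78.
- State that preterm birth will be reported as an estimate with its confidence interval, and that a non-significant result will not be read as absence of effect. The detail of that reading can go in the analysis plan.

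The cost is wording only. No participants are added and no test or outcome changes. The stated power becomes less favourable.

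### The unqualified claim of adequate power conflicts with the protocol's own figures for preterm birth (about 14% power at the cited smoking effect), and the low-birth-weight column that appears to support it is miscalculated

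*Protocol article*

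**What the plan says.** Table 2 of the protocol article lists preterm birth, low birth weight and doctor-diagnosed wheeze among the primary outcomes, and the text introducing it says: "The primary outcomes outlined in Table 2 have informed the sample size calculation".

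Under Power calculations and rationale, Table 3 gives odds ratios "detectable at a power of 80%, with a type I error rate of 0.05". On the method it says: "These assume use of simple uncorrected Chi-square test or" t tests. On allocation: "We plan to collect three equally sized groups". At 400 per group the tabulated detectable ORs are 1.80 (wheeze, 10% baseline), 2.04 (preterm birth, 6.2%) and 1.74 (low birth weight, 5%).

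The text after Table 3 supplies the effects to compare with it, all of them effects of smoking: 1.8 (95% CI 1.35 to 2.53) for wheeze, 1.75 (1.42 to 2.10) for low birth weight and, for preterm birth, "The odds ratio for PTB conferred by smoking is 1.27" (1.20 to 1.33). The conclusion follows: "we propose to recruit 1200 participants (400 smokers, 400 vapers and 400 non-smoker, non-vaper controls", and this is said "to generate adequate power and precision to answer our research questions". No outcome is excepted.

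Both hypotheses concern vapers. The first expects worse outcomes than in non-smokers. The second expects better outcomes than in smokers: "Women who vape during pregnancy will be less likely to have a preterm birth and their infants will have a higher birth weight".

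**The concern.** For preterm birth, the tabulated detectable OR of 2.04 lies far above the upper confidence limit (1.33) of the effect quoted a few lines later. The conclusion about power does not follow from the figures in front of it.

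For low birth weight, the tabulated 1.74 seems to match the cited 1.75. But the 5% outcome is shown with smaller detectable ORs than the commoner 6.2% outcome at every sample size, and smaller than the 10% outcome at 300 and 400 per group. With the same test and sample size, a rarer outcome in this range needs a larger OR.

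The effects set against Table 3 are all smoker-versus-control effects, while the study's questions are vaper-versus-control and vaper-versus-smoker. Table 3 uses only the general baseline rates, so nothing is computed for vapers against smokers.

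At stake is how a non-significant result is read. The article expects its findings to inform guidelines. With adequate power on record, p>0.05 for preterm birth or low birth weight could be taken as evidence that vaping is harmless, or no better than smoking, when the study could not have told these apart at effects of smoking size.

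**Working it through.** **Inputs, all from the protocol article.** n = 400 per group; alpha 0.05; target power 80%; uncorrected chi-square test; baselines 10%, 6.2% and 5%; smoking ORs 1.8, 1.75 and 1.27. Sidedness is not stated. Two-sided testing is used here because it reproduces Table 3; one-sided does not.

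**Formulas.** p2 = OR·p1 / (1 − p1 + OR·p1); d = |p2 − p1|; p̄ = (p1 + p2)/2; s0 = √[2p̄(1 − p̄)/n]; s1 = √{[p1(1 − p1) + p2(1 − p2)]/n}. Power = Φ[(d − 1.96·s0)/s1] + Φ[(−d − 1.96·s0)/s1].

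**Step 1: reproduce Table 3** (solve for the OR that gives 80% power).

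| Outcome | | n=100 | n=200 | n=300 | n=400 |
|---|---|---|---|---|---|
| Wheeze, 10% | stated | 3.00 | 2.25 | 1.96 | 1.80 |
| | computed | 2.99 | 2.25 | 1.96 | 1.81 |
| Preterm birth, 6.2% | stated | 3.62 | 2.63 | 2.24 | 2.04 |
| | computed | 3.63 | 2.62 | 2.24 | 2.04 |
| Low birth weight, 5% | stated | 3.19 | 2.26 | 1.91 | 1.74 |
| | computed | 4.01 | 2.84 | 2.40 | 2.17 |

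Two columns reproduce, so the method is the authors'. The third does not. At n = 400, one-sided testing (2.01), a continuity correction (2.24), a relative risk in place of an OR (2.05) and unequal allocation (2.00 or 2.47) do not recover 1.74 either.

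**Step 2: power at the cited smoking ORs, smokers against controls, n = 400.**

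- Preterm birth: p2 = 0.07874/1.01674 = 0.0774; d = 0.01544; s0 = 0.01801; s1 = 0.01800. (0.01544 − 0.03530)/0.01800 = −1.10, giving 0.135; the opposite tail adds 0.002. Power is about 14%. At OR 1.20 it is 10% and at OR 1.33 it is 18%. One-sided it would be about 22%. The n per group for 80% power is [1.96·√(2p̄(1 − p̄)) + 0.8416·√(p1(1 − p1) + p2(1 − p2))]²/d², about 4,270.
- Low birth weight: p2 = 0.0875/1.0375 = 0.0843; d = 0.03434; s0 = 0.01770; s1 = 0.01766. (0.03434 − 0.03469)/0.01766 = −0.02. Power is about 49% (21% at OR 1.42, 76% at OR 2.10). 80% needs about 834 per group.
- Wheeze: p2 = 0.18/1.08 = 0.1667; d = 0.06667; s0 = 0.02404; s1 = 0.02392. (0.06667 − 0.04711)/0.02392 = 0.82. Power is about 79% (27% at OR 1.35, above 99% at OR 2.53).

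Simulating the uncorrected chi-square test gives 13.6%, 49.5% and 79.6% for preterm birth, low birth weight and wheeze.

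**Step 3: the vaper contrasts.** OR(vaper/control) × OR(smoker/vaper) = OR(smoker/control). If both hypotheses hold, both factors on the left exceed 1, so each is smaller than the smoking OR.

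The article gives no vaping effect. As an illustration only, assume the point-estimate smoking ORs and place vapers 25%, 50% or 75% of the way from controls to smokers on the log-odds scale. Power against controls / against smokers is then:

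| Outcome | 25% | 50% | 75% |
|---|---|---|---|
| Wheeze | 10% / 57% | 26% / 31% | 53% / 12% |
| Low birth weight | 7% / 32% | 15% / 18% | 29% / 8% |
| Preterm birth | 5.5% / 10% | 7% / 7% | 10% / 5.6% |

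**Step 4: detectable OR for vapers against smokers.** At assumed smoker rates of 16.7%, 7.7% and 8.4% (from step 2), the ORs giving 80% power at 400 per group are about 0.55 (wheeze), 0.40 (preterm birth) and 0.42 (low birth weight).

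**Step 5: what a null preterm-birth result would look like.** With 6.2% in both groups there are 24.8 events and 375.2 non-events per group. SE(log OR) = √[2(1/24.8 + 1/375.2)] = 0.293, so the 95% CI is about exp(±1.96 × 0.293) = 0.56 to 1.78. It contains the cited smoking effect of 1.27.

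**The case against.** Both conflicting preterm-birth figures are printed openly, this is an observational cohort, and the sentence claims precision as well as power. All true, but disclosing 2.04 and 1.27 does not make the conclusion drawn from them correct.

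The research questions also include neurocognitive outcomes. Table 4's detectable standardised mean difference of 0.20 at 400 per group reproduces (0.198) and sits at the edge of the cited 0.2 to 0.4 range. Wheeze is close to 80% at its smoking benchmark. This stands: a reader might infer that the whole study is underpowered, and the article does not support that.

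A reader might also infer that the vaper contrasts must be smaller than the smoking effect. The hypotheses give direction without size, the obstetric objective leaves open whether risk is higher or lower, and the article says good data on vaping are lacking. The bound holds only if both hypotheses hold. The illustration in step 3 adds an assumed placement and fixed point-estimate ORs; at the upper limit for wheeze (2.53), power would be higher.

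Nor is a non-significant result likely whatever the truth. A true OR against controls of about 2.04 for preterm birth, or 2.17 for low birth weight, would be detected with 80% power.

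Finally, nothing in the article says that a null result will be read as safety, and choosing one confirmatory outcome is commonly left to an analysis plan. Neither is claimed here.

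**Conclusion.** The claim of adequate power is wrong as written and must be qualified. For preterm birth the contradiction lies within the article and needs no outside figure: a detectable OR of 2.04 against a cited 1.27, with power of about 14% (10% to 18% over the cited CI). For low birth weight the apparent support comes from a wrong table column; power at the cited OR is about 49%. Of the three binary primary outcomes, only wheeze roughly meets its smoking benchmark, at about 79%.

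These figures rest on the article's baselines, ORs and test, two-sided 0.05, complete data and no adjustment for several outcomes or contrasts. Lost data or such an adjustment would lower them.

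For the vaper contrasts the conclusion is conditional. If both hypotheses hold, each has a smaller OR than the benchmark. With vapers placed 25% to 75% of the way, power runs over about 10% to 57% (wheeze), 7% to 32% (low birth weight) and 5.5% to 10% (preterm birth). That range depends on the assumed placement and is not a property the article states.

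**What to change.** 1. Replace the blanket sentence with a statement by outcome: about 79% power for wheeze, 49% for low birth weight and 14% for preterm birth at the cited smoking ORs, with 400 per group.
2. Correct the low-birth-weight column of Table 3 to about 4.01, 2.84, 2.40 and 2.17.
3. Add detectable ORs for vapers against smokers: about 0.55 (wheeze), 0.40 (preterm birth) and 0.42 (low birth weight), with the assumed smoker rates of 16.7%, 7.7% and 8.4% shown. Say that the existing rows apply to comparisons with controls.
4. State that preterm-birth and low-birth-weight contrasts will be reported as estimates with 95% CIs, and that p>0.05 will not be read as no difference.

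The cost is some rewording, one corrected column and one added set of table entries. No extra participants and no change of design or outcomes are needed. The downside is a less favourable statement of power.
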